## Abstract

**Background::**

We conduct this randomized controlled trial protocol for the comparison of the influence of the hydrocolloid dressing and polyurethane foam dressing in the treatment of pressure ulcers (PUs) patients.

**Methods::**

This study will be implemented from February 2021 to February 2022 at Hangzhou Geriatric Hospital. The experiment was granted through the Research Ethics Committee of Hangzhou Geriatric Hospital (C5259033). Criteria for inclusion: patients older than 18 years of age who have been diagnosed with PU. If the patient suffers from more than a PU, only the ulcer with largest diameter is evaluated.

Criteria for exclusion:

The major result is rate of PU healing or ulcer epithelialization tissue. The secondary result is the changes in the area of ulcer in cm and cost-effectiveness. The analysis of all the data are conducted with the software of IBM SPSS Statistics for Windows, version 20 (IBM Corp., Armonk, NY).

**Results::**

Table 1 will show the comparison of clinical outcomes between 2 groups.

**Conclusion::**

This study can develop an evidence-based protocol to identify optimal dressings for patients with PUs.

**Trial registration number::**

researchregistry6294

## Introduction

1

Pressure ulceration is an important problem of healthcare in the world, placing a great burden on the resources of healthcare.^[1,2]^ Pressure ulcers (PUs) are usually hard to cure and can cause a serious negative impact on the life quality and mortality of patients.^[3,4]^ The generation of PU is greatly affected via a variety of risk factors, involving various conditions that result in malnutrition, the lack of sensation, and hypermobility.^[5,6]^ In recent years, the epidemiological data related to PUs in the United States has been relatively limited, with the annual incidence estimated at between 1 million and 3 million.^[7]^ Among all the inpatients, the reported prevalence varies significantly, with a total of 5% to 15% of patients affected, but patients’ proportion affecting in ICU is still high.^[8]^ Despite PUs are generally caused by the poor condition of health and some other diseases, in many cases it can be avoided. Thus, our target is to prevent the PU, which is all more important in view of the high treatment cost and challenges. For the effective prevention approaches, its fundamental elements involve proper nutrition, the use of appropriate support surfaces, frequent repositioning, and moisture management.^[9–11]^

Polyurethane foam dressings have been developed for many years and have been utilized to treat the wounds with mild to moderate exudate.^[12]^ It is easy to utilize and then remove and is beneficial to the process of healing. Recent studies have reported that polyurethane foam dressings were effective in treating PUs. Other articles also recommended to prevent PUs by using a hydrocolloid dressing, including ulcers caused by noninvasive ventilation.^[13]^ So far, the clinical trials and systematic reviews have not provided sufficient evidence to demonstrate their effectiveness. Therefore, we conduct this randomized controlled trial protocol for the comparison of the influence of the hydrocolloid dressing and polyurethane foam dressing in the treatment of PUs patients.

## Methods

2

This study will be implemented from February 2021 to February 2022 at Hangzhou Geriatric Hospital. The experiment was granted through the Research Ethics Committee of Hangzhou Geriatric Hospital (C5259033) and recorded in research registry (researchregistry6294). Sequence of random numbers is generated by a computer. Sequentially numbered sealed opaque envelopes are used for the concealment of random numbers. All the patients taking part in our experiment are randomly divided to polyurethane foam dressing or hydrocolloid dressing group, and each group includes 48 participants.

### Inclusion and exclusion criteria

2.1

Criteria for inclusion: patients older than 18 years of age who have been diagnosed with PU. If the patient suffers from more than a PU, only the ulcer with largest diameter is evaluated. Criteria for exclusion:

(1)hypersensitivity or allergy to the substances in dressings;(2)patients with diabetic foot or venous ulcers; and(3)serious disease.

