### Intervention

2.2

The standardized preventive intervention will be given to all patients for the reduction of pressure and experience a process of PU healing treatment.

The process of healing cure involves a total of 3 aspects:

(1)Every time the research dressing is changed, wound needs to be washed. The skin cleaners and local antiseptics should be avoided because they are cytotoxic to new granulating tissue.(2)The process of drying must also be delicate. The rough materials may cause minor wounds in wound bed, thereby interfering with the process of healing and enhancing the infection risk. The wound bed should be moist and the edges of the wound should be clean and dry. Care should be taken to avoid damaging healthy tissue during cleansing and drying procedures.(3)The prevention of bacterial infection should be strengthened. The aseptic techniques should be utilized wherever possible, involving utilizing the clean gloves. Proper debridement and healing procedures can reduce the infection risk. If the patient suffers from more than a PU, the most contaminated ulcer should be left for treatment at the end.

Polyurethane foams: These dressings have the hydrophilic structure and are derived from polyurethane. They have a high exudates absorption and a high autolysis debridement capacity, and can prevent the wound bed from drying, leaving no decomposition, and residuals. Furthermore, they avoid odors, stains and leakages, keep the skin around the wound intact, and do not cause traumas during removal. These dressings are suitable at all the PU stages. When PU infections occur, the frequent monitoring and modification may be necessary.

Hydrocolloids: These dressings are composed of carboxymethyl cellulose and some other water active compounds, adhesion substances, or hydrocolloids to offer the absorption capacity. These dressings are covered with a layer of polyurethane to make them semi occlusive or occlusive properties. Furthermore, they absorb exudates and necrotic residuals by forming a gel with special color and odor characteristics, creating a slightly acid environment with bacteriostatic properties. In addition, they decrease the friction. These dressings are suitable for uninfected PU.

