### Outcome

2.3

The major result is rate of PU healing or ulcer epithelialization tissue. The secondary result is the changes in the area of ulcer in cm and cost-effectiveness.

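### The stated analysis of healing ignores baseline ulcer stage and area although eligibility limits neither, which costs precision at 48 per arm

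*Protocol article*

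**What the plan says.** Section 2.1 of the protocol article (Inclusion and exclusion criteria) admits "patients older than 18 years of age who have been diagnosed with PU". For a patient with several ulcers, "only the ulcer with largest diameter is evaluated". The exclusions are allergy to dressing materials, "patients with diabetic foot or venous ulcers", and serious disease. None restricts the stage, depth or area of a pressure ulcer.

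Section 2 (Methods) says of allocation that "Sequence of random numbers is generated by a computer", that sealed opaque numbered envelopes conceal it, and that "each group includes 48 participants". Stratification is neither described nor ruled out.

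Section 2.3 (Outcome) states: "The major result is rate of PU healing or ulcer epithelialization tissue". Change in ulcer area is a secondary outcome.

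Section 2.4 (Statistical analysis) presents t tests and chi-square tests, at P below .05, as the methods for all the data. The Table 1 shell agrees: one column per arm, one P value per row, and no adjusted or stage-specific result.

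**The concern.** Small superficial ulcers and large deep ones can both enter, and their chances of healing are likely to differ a great deal. Stage and area can be recorded before the envelope is opened, and area has to be measured at baseline anyway because change in area is an outcome. The stated analysis uses neither.

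Two things are at stake. First, variation in healing that severity could explain stays in the error term, so power is lost in every trial of this size. Second, if the arms happen to differ in severity, the crude difference in healing carries that imbalance, and the stated analysis has no means of correcting it.

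**Working it through.** **Inputs from the article.** 48 per arm; significance at .05 (two-sided assumed); crude two-group tests. Healing is taken as a yes/no outcome compared by chi-square. Section 2.4 prints the two variable types the wrong way round, which is a separate matter.

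**Inputs assumed.** The article gives no severity mix, healing rates or power calculation, so the 48 per arm cannot be reproduced. I take a severe share q of 0.3 to 0.5, a healing gap between mild and severe ulcers of 30 to 60 points, and allocation that ignores severity.

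**1. What 48 per arm can detect.** For two proportions, 80% power needs a difference of 28.5 points at base rates of 30% or 40%, 27.5 at 50%, and 25.5 at 60%. There is little precision to spare.

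**2. How large chance imbalance is.** The SD of the between-arm difference in severe share is sqrt(2q(1-q)/48).
- q = 0.3: sqrt(2 × 0.3 × 0.7/48) = 0.094
- q = 0.5: sqrt(2 × 0.5 × 0.5/48) = 0.102

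Exact probabilities, from the difference of two Binomial(48, q) counts:

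| Imbalance at least | q = 0.3 | q = 0.5 |
|---|---|---|
| 10 points | 31.6% | 35.8% |
| 15 points | 9.4% | 12.5% |
| 20 points | 3.4% | 5.2% |

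**3. What an imbalance does to the crude difference.** Shift = imbalance × healing gap. It runs from 0.15 × 0.30 = 4.5 points to 0.20 × 0.60 = 12 points.

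**4. False-positive rate with no true effect.** Simulation, 400,000 trials per scenario; q = 0.3 or 0.5; healing mild/severe 0.6/0.3, 0.7/0.2 or 0.8/0.2. The crude chi-square (no continuity correction) is set against a Cochran-Mantel-Haenszel (CMH) test stratified by severity.

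| Trials considered | Crude | CMH |
|---|---|---|
| All | 5.0-5.2% | 5.0% |
| Imbalance at least 15 points | 8-18% | 4.9-5.0% |
| Imbalance at least 20 points | 10-26% | 4.9-5.2% |

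**5. Power.** Same simulation with q = 0.5 and the same added effect in both severity groups. The last two columns cover only trials in which the better arm has at least 15 points more severe ulcers.

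| Control healing mild/severe, effect | Crude, all | CMH, all | Crude, imbalanced | CMH, imbalanced |
|---|---|---|---|---|
| 0.6/0.3, +20 points | 51% | 54% | 28% | 52% |
| 0.7/0.2, +20 points | 51% | 63% | 14% | 60% |
| 0.6/0.1, +25 points | 71% | 83% | 30% | 80% |

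The gain over all trials is 3, 12 and 12 points.

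**6. A moderate case by hand.** Take 40% severe, with healing of 20% in severe and 60% in mild ulcers. Overall healing is 0.4 × 0.2 + 0.6 × 0.6 = 0.44. The crude SE of the difference is sqrt(2 × 0.44 × 0.56/48) = 10.1 points. The within-severity variance is 0.4 × 0.2 × 0.8 + 0.6 × 0.6 × 0.4 = 0.208, which gives an SE of sqrt(2 × 0.208/48) = 9.3 points, about 8% smaller. The SD of the severity imbalance is sqrt(2 × 0.4 × 0.6/48) = 10 points. An imbalance of that size shifts the crude difference by 0.10 × 0.40 = 4 points, or 0.4 of the crude SE.

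**The case against.** The strongest reply is that chance imbalance is not bias. The crude test's standard error already allows for it, and step 4 confirms that the error rate over all randomizations is about 5%. This stands. A reader might infer that the crude test is invalid or biased. It is not: the raised error appears only after conditioning on an imbalance that has occurred. In the moderate case the gain is also modest.

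A reader might also infer that allocation is unstratified. The article does not say so, and a condensed article commonly leaves blocks and strata to the full protocol. Equal groups of exactly 48 even hint at some restriction, since simple randomization of 96 patients gives a 48/48 split only about 8% of the time. The imbalance figures above are therefore conditional on unstratified allocation. If allocation is stratified by severity, large imbalances become unlikely, but the stated crude tests would still ignore the strata.

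The sentence "These dressings are suitable at all the PU stages" might be read as saying that the trial will treat every stage. It stands in the description of the foam product, and the hydrocolloid description says only "These dressings are suitable for uninfected PU". The breadth of the population rests on section 2.1 alone.

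Finally, covariate adjustment may be specified in an analysis plan that is not shown. That would settle the point. But section 2.4 and the Table 1 shell do more than stay silent: they state a crude comparison as the method.

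**Conclusion.** The point holds as one about precision and protection against an unlucky draw. Eligibility is open on stage and size, the stated analysis is crude, and a better analysis is available at almost no cost. Across the assumed scenarios, a severity-stratified test adds about 3 to 12 points of power. It also holds the false-positive rate near 5% in the 9-13% of unstratified trials whose arms differ by at least 15 points in severe share, where the crude test gives 8-18%.

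These figures rest on assumed severity shares and healing rates. The power figures cover gaps of 30 and 50 points with half the ulcers severe. With a weak gap the gain is small. The simulation used a two-level severity factor, so it does not show what adding baseline area would contribute. This is a worthwhile improvement to the plan; nothing here makes the planned test invalid.

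**What to change.** In section 2.4, prespecify:

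- **Primary outcome (healed or not):** logistic regression on arm, baseline stage (superficial or deep) and log baseline area, reporting a standardised (adjusted) risk difference with 95% CI. A Mantel-Haenszel analysis by stage would be a simpler alternative, but it cannot take area as a continuous covariate.
- **Change in ulcer area:** ANCOVA with baseline area as covariate.
- **Crude tests:** keep as supportive analyses.
- **Allocation:** if the scheme is in fact stratified, include its strata in the model.

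Fix this before any outcome is seen by arm. It is an analysis change only and can be made even if randomization has started. The cost is recording stage at baseline and a little more analysis work; baseline area is needed in any case.

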### Intervention

2.2

The standardized preventive intervention will be given to all patients for the reduction of pressure and experience a process of PU healing treatment.

The process of healing cure involves a total of 3 aspects:

(1)Every time the research dressing is changed, wound needs to be washed. The skin cleaners and local antiseptics should be avoided because they are cytotoxic to new granulating tissue.(2)The process of drying must also be delicate. The rough materials may cause minor wounds in wound bed, thereby interfering with the process of healing and enhancing the infection risk. The wound bed should be moist and the edges of the wound should be clean and dry. Care should be taken to avoid damaging healthy tissue during cleansing and drying procedures.(3)The prevention of bacterial infection should be strengthened. The aseptic techniques should be utilized wherever possible, involving utilizing the clean gloves. Proper debridement and healing procedures can reduce the infection risk. If the patient suffers from more than a PU, the most contaminated ulcer should be left for treatment at the end.

Polyurethane foams: These dressings have the hydrophilic structure and are derived from polyurethane. They have a high exudates absorption and a high autolysis debridement capacity, and can prevent the wound bed from drying, leaving no decomposition, and residuals. Furthermore, they avoid odors, stains and leakages, keep the skin around the wound intact, and do not cause traumas during removal. These dressings are suitable at all the PU stages. When PU infections occur, the frequent monitoring and modification may be necessary.

Hydrocolloids: These dressings are composed of carboxymethyl cellulose and some other water active compounds, adhesion substances, or hydrocolloids to offer the absorption capacity. These dressings are covered with a layer of polyurethane to make them semi occlusive or occlusive properties. Furthermore, they absorb exudates and necrotic residuals by forming a gel with special color and odor characteristics, creating a slightly acid environment with bacteriostatic properties. In addition, they decrease the friction. These dressings are suitable for uninfected PU.

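### An ulcer infected at entry can be randomised to hydrocolloid, which the protocol describes as suitable only in terms of uninfected ulcers

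*Protocol article*

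**What the plan says.** Three parts of the protocol article bear on this.

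- **Eligibility (section 2.1).** The trial admits "patients older than 18 years of age who have been diagnosed with PU". The three numbered exclusions are sensitivity to dressing components, diabetic foot or venous ulcers, and serious disease, which is not defined. None refers to infection of the ulcer. For a patient with several ulcers, "only the ulcer with largest diameter is evaluated".
- **Allocation (section 2).** "All the patients taking part in our experiment are randomly divided to polyurethane foam dressing or hydrocolloid dressing group", with 48 in each group. On concealment: "Sequentially numbered sealed opaque envelopes are used for the concealment of random numbers". No restriction or stratum by infection status is given.
- **Suitability (section 2.2).** Of hydrocolloids the article says: "These dressings are covered with a layer of polyurethane to make them semi occlusive or occlusive properties". It credits them with "creating a slightly acid environment with bacteriostatic properties", and the paragraph ends: "These dressings are suitable for uninfected PU". The foam paragraph speaks of suitability by ulcer stage and adds a caution: "When PU infections occur, the frequent monitoring and modification may be necessary". The hydrocolloid paragraph has no counterpart to that caution.

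**The concern.** The entry criteria and the description of one of the two dressings do not fit together. A patient whose largest ulcer is already infected meets section 2.1, must be randomised under section 2, and may be assigned a dressing whose stated use in section 2.2 does not include that ulcer. Staff would then have to choose between the envelope and the protocol's own account of the dressing, with nothing in the text to guide them.

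What is at stake is the safety of those patients and the coherence of the eligible population. The comparison between arms is not biased by this: randomisation happens without regard to infection, so infected ulcers are expected in both groups in equal proportion.

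**Working it through.** **Step 1: the text.** Take an adult whose largest pressure ulcer is infected on the day of screening.

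| Question | Source | Answer |
|---|---|---|
| Eligible? | 2.1, inclusion | Yes: over 18, diagnosed ulcer |
| Excluded? | 2.1, exclusions | No: none of the three concerns infection of the ulcer |
| Is this the assessed ulcer? | 2.1 | Yes: chosen by diameter alone |
| Can hydrocolloid be assigned? | 2 | Yes: every participant is randomised to one of the two dressings |
| Is hydrocolloid described as suitable for it? | 2.2 | No: the suitability named is for uninfected ulcers |

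The infection-prevention text in 2.2 does not change this. It concerns aseptic care and debridement during treatment, not entry. The bacteriostatic property does not change it either, because the same paragraph claims that property and still states suitability in terms of uninfected ulcers.

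**Step 2: how many patients could be affected.** The article has no figure of its own to reproduce. The only input taken from it is n = 48 in the hydrocolloid group (section 2). The share p of index ulcers infected at entry is not given, so values of 1%, 5%, 10% and 20% are assumed, with patients independent.

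- Expected number = 48p.
- Central 95% range = the 2.5% and 97.5% quantiles of Binomial(48, p).
- Chance of none = (1 − p)^48.

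| Assumed p | Expected number | Central 95% range | Chance of none |
|---|---|---|---|
| 1% | 48 × 0.01 = 0.48 | 0–2 | 0.99^48 = 0.617 |
| 5% | 48 × 0.05 = 2.4 | 0–6 | 0.95^48 = 0.085 |
| 10% | 48 × 0.10 = 4.8 | 1–9 | 0.90^48 = 0.0064 |
| 20% | 48 × 0.20 = 9.6 | 5–15 | 0.80^48 = 0.00002 |

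**Step 3: thresholds.** At least one such allocation has probability 0.5 when p = 1 − 0.5^(1/48) = 0.0143, and probability 0.95 when p = 1 − 0.05^(1/48) = 0.0605.

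**Step 4: recruitment cost of an exclusion.** Patients to assess for 96 randomised = 96/(1 − p), rounded up.

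| Assumed p | Patients to assess | Additional |
|---|---|---|
| 1% | 97 | 1 |
| 5% | 102 | 6 |
| 10% | 107 | 11 |
| 20% | 120 | 24 |

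**The case against.** The strongest reply is that the suitability sentence is a general product description, set among remarks on composition, absorption and odour. It does not say that hydrocolloid suits uninfected ulcers only, and it names no contraindication. That is right, and the point should claim no more than that the protocol does not describe the dressing as suitable for infected ulcers. The sentence nevertheless stands in the Intervention section and is the only statement there of which ulcers hydrocolloid suits.

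A second reply is that a short article condenses a fuller protocol, which may list more criteria. It may. But the mismatch lies between two things this article prints: a numbered exclusion list that does not present itself as a selection, and a suitability statement that the list does not respect. The undefined exclusion for serious disease names a condition of the patient and does not naturally cover a local wound infection.

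Third, the article does not show that harm follows from dressing an infected ulcer this way, and it gives no infection rate. Both stand. The counts above are purely conditional, span a twenty-fold range, and the thresholds would be the same for any event among 48 patients.

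Fourth, excluding an infected index ulcer leaves open infection that arises after allocation, and infected ulcers other than the index one if these receive the allocated dressing, which the text does not say. This also stands; the point is limited to the index ulcer at entry. Foam is not declared suitable for infected ulcers either: its wide suitability concerns stage, and its only remark on infection is a caution.

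**Conclusion.** The concern holds. Sections 2, 2.1 and 2.2 taken together allow an index ulcer infected at entry to be assigned to a semi-occlusive or occlusive dressing that the protocol does not describe as suitable for it. This rests on the printed text alone.

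Its frequency cannot be derived from the document. Under assumed infected shares of 1% to 20%, the expected number in the hydrocolloid group runs from about 0.5 to 9.6; at least one case is more likely than not above a share of about 1.4% and at least 95% likely from about 6.1%. These figures show what the gap allows, not how often it will occur. The point should be fixed because it touches patient safety and is cheap to close. It does not call the randomised comparison, the endpoint or the sample size into question. Confidence is medium, because the suitability sentence is descriptive and a fuller protocol may exist.

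**What to change.** Add a fourth exclusion to section 2.1: a clinically infected index ulcer, meaning the largest-diameter ulcer, with infection status checked and recorded before the envelope is opened. Checking first keeps the decision independent of the allocation.

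The cost is one line of eligibility wording by amendment, a bedside check, the additional screening shown above (1 to 24 patients under the assumed shares), and results that do not extend to ulcers infected at entry. The alternative, a rule for switching dressing after allocation, would keep the wider population but would move patients off their assigned dressing, so the exclusion is preferable for infection present at entry.
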